### Data analysis

#### Power of the trial: Sample size and power calculation.

We calculated the required sample size to detect a statistically significant difference in the Short Physical Performance Battery (SPPB) scores following the intervention. A significance level (α) of 5% was assumed, with a correlation coefficient (ρ) of 0.5 between the pre- and post-intervention values, and a standard deviation (σ) of 2.5 for the SPPB. The required sample size to achieve a statistical power of 90% and detect a clinically significant minimum difference of one point in the post-intervention SPPB score was determined to be 102 patients per group. To account for an anticipated dropout rate of 30% during follow-up, the final required sample size increased to 148 patients per group, resulting in a total of 296 participants across both groups. This calculation implies the need to recruit approximately 50 patients per group at each of the three participating hospitals (N = 300).

### Statistical methods

First, a comprehensive descriptive analysis will be conducted on the entire sample and within individual groups. For continuous variables, measures of central tendency and dispersion will be calculated based on their distribution, utilising either the mean and standard deviation or the median and interquartile range (IQR). Qualitative variables will be summarised as frequencies and percentages, with corresponding confidence intervals to estimate the overall prevalence. Baseline characteristics between the treatment and control groups will be compared using the Student’s t-test or the Mann–Whitney U test for quantitative variables, and the Chi-square test or Fisher’s exact test for qualitative variables.

The impact of the intervention on various outcome measures will be assessed using ANCOVA or linear mixed-effects models with a random intercept for continuous variables. Logistic regression models and analyses of rate or proportion differences will be applied to outcomes such as falls, mortality, and institutionalisation. In the event of significant baseline imbalances in any independent variable, sensitivity analyses will be conducted to adjust for these differences in the final analysis. No imputation of missing data will be conducted.

The analysis will adhere to the intention-to-treat principle, and additional per-protocol analyses will be performed as a secondary sensitivity measure. Statistical significance will be determined at a threshold of 0.05 for all tests. Data analysis will be conducted using SPSS (version 25.0) and R software (version 4.0).

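### The 102 per group assumes a baseline-adjusted SPPB analysis, but the Statistical methods section does not commit to one, and one random-intercept model that it permits has about 81% power

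*Protocol article*

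**What the plan says.** The sample-size section of the Protocol article (Power of the trial) takes α = 5% and an SPPB standard deviation of 2.5. On the link between baseline and follow-up scores, it works "with a correlation coefficient (ρ) of 0.5 between the pre- and post-intervention values". The target is 90% power to "detect a clinically significant minimum difference of one point in the post-intervention SPPB score". The resulting number per arm "was determined to be 102 patients per group", raised to 148 per group for 30% dropout. No visit is attached to the post-intervention score.

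The Statistical methods section says the effect on the outcome measures will be "assessed using ANCOVA or linear mixed-effects models with a random intercept for continuous variables". It does not say which of the two applies to SPPB, whether baseline SPPB enters as a covariate or as one of the responses, or which contrast is tested. Its only explicit statement on adjustment is a sensitivity analysis if baseline imbalance is found. The Data collection section defines the primary outcome as SPPB at discharge, one month and three months relative to baseline, and does not single out a visit.

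**The concern.** The pre-post correlation of 0.5 reduces the sample size only if the analysis uses the baseline score efficiently. If the primary analysis does not, the trial is sized for a test it does not run. The outcome is described relative to baseline over four visits, so a natural reading of the mixed-model option is a group-by-visit test with all four visits as responses. That test estimates a difference in mean change and does not get the variance reduction on which the 102 rests.

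A second issue concerns the covariance. A model whose only random term is a patient intercept assumes the same variance at every visit and the same correlation between every pair of visits. Here the baseline is taken soon after acute admission and the later visits after recovery at home, so equality is a strong assumption. If it fails, the standard error of a contrast at one visit can be too small or too large.

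**Working it through.** **Inputs.** From the sample-size section: α = 0.05, power 0.90, difference 1 point, σ = 2.5, ρ = 0.5, n = 102 per group. Sidedness is not stated (the Statistical methods section says only "Statistical significance will be determined at a threshold of 0.05 for all tests"); two-sided is assumed here.

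**1. Reproducing the 102.** n per group = 2 × (1.95996 + 1.28155)² × σ² × f / 1² = 2 × 10.507 × 6.25 × f = 131.3 × f, where f is the variance factor of the analysis.

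- Follow-up score only: f = 1, so 131.3, i.e. 132.
- Change from baseline: f = 2(1 − 0.5) = 1, so again 132.
- Baseline-adjusted: f = 1 − 0.5² = 0.75, so 98.5, i.e. 99 (100 with the t distribution).

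The one-sided equivalents are 108, 108 and 81. Only the two-sided adjusted figure comes close to 102.

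**2. Power at 102 per group.** SE = 2.5 × √(2f/102).

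- f = 0.75: SE = 0.303; 1/0.303 − 1.96 ≈ 1.34; power 91.0% (90.7% with t).
- f = 1: SE = 0.350; 1/0.350 − 1.96 ≈ 0.90; power 81.5% (81.1% with t).

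**3. Random-intercept models the wording permits.** Baseline is a response, all correlations are 0.5, 102 per group are complete, and normal quantiles are used:

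| Baseline means | Contrast | SE | Power |
|---|---|---|---|
| Free in each group | 3 months vs baseline | 0.350 | 81.5% |
| Constrained equal | 3 months | 0.303 | 91.0% |
| Free in each group | Average of three visits vs baseline | 0.286 | 93.8% |
| Constrained equal | Average of three visits | 0.226 | 99.3% |

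The averaged rows assume that the one-point effect is present at all three visits.

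**4. Partial follow-up.** Take 148 randomised per group and assume that 10% of them are lost before each follow-up visit, so 70% complete all four. The free-baseline 3-month contrast then has SE 0.330 and power 85.8%; the constrained one has SE 0.296 and power 92.2%. The dropout pattern is an assumption; the protocol gives only the 30% total.

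**5. Standard error under a random intercept.** With complete data, equal variances and free means, the model in effect uses the average ρ̄ of the six pairwise correlations. For a visit-minus-baseline contrast, model SE / true SE = √[(1 − ρ̄)/(1 − ρ₀ₖ)], where ρ₀ₖ is the true correlation of that visit with baseline. Type I error = 2Φ(−1.96 × ratio). Every pattern below except the first is an assumption:

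| Correlation of baseline with V1, V2, V3 | V1–V2, V1–V3, V2–V3 | ρ̄ | Contrast | Ratio | Type I error |
|---|---|---|---|---|---|
| 0.5, 0.5, 0.5 | 0.5, 0.5, 0.5 | 0.500 | 3 months | 1.00 | 5.0% |
| 0.7, 0.6, 0.5 | 0.7, 0.6, 0.7 | 0.633 | 3 months | 0.86 | 9.3% |
| 0.7, 0.6, 0.5 | 0.7, 0.6, 0.7 | 0.633 | Discharge | 1.11 | 3.0% |
| 0.5, 0.4, 0.3 | 0.6, 0.5, 0.7 | 0.500 | 3 months | 0.85 | 9.8% |
| 0.5, 0.5, 0.5 | 0.7, 0.7, 0.7 | 0.600 | 3 months | 0.89 | 8.0% |
| 0.5, 0.5, 0.5 | 0.8, 0.8, 0.8 | 0.650 | 3 months | 0.84 | 10.1% |
| 0.4, 0.5, 0.6 | 0.5, 0.5, 0.5 | 0.500 | 3 months | 1.12 | 2.8% |

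Baseline adjustment alone does not remove this. Under the second pattern with baseline by visit as a covariate, the residual variances at the three visits are 1 − 0.7² = 0.51, 1 − 0.6² = 0.64 and 1 − 0.5² = 0.75 (times σ²), average 0.633. The ratio at 3 months is √(0.633/0.75) = 0.92, which gives a type I error of about 7.2%.

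**The case against.** The strongest objection is that the 81% model is only one reading. The protocol does not say that baseline is a response or that the test is group by visit. A random-intercept model on the three follow-up visits with baseline SPPB as a covariate fits the same words, and the use of ρ in the sample size suggests that adjustment was intended. The sentence covers all continuous outcomes, so its *or* may simply separate outcomes measured once from those measured repeatedly. An SAP, not shown, may already fix the model.

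Much of this stands, and it limits the point. Three stronger readings are not supported:

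- **A reader might infer that 90% power requires baseline as a covariate, or that a mixed model is underpowered as such.** Constraining the baseline means keeps 91.0%, and averaging over visits exceeds 90% even with free means. The loss comes from free baseline means combined with a single-visit contrast.
- **A reader might infer that the random-intercept test is anti-conservative.** The documents give one correlation, 0.5. If it holds for every pair of visits and the variances are equal, the test is correct. Under other patterns the error goes either way.
- **A reader might infer that the model will be picked after the data are seen.** Nothing in the protocol says so.

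The objection does not remove the mismatch. The protocol does address the model: it states two alternatives, and the wording admits a form that falls short of the power claimed in the section before it.

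**Conclusion.** The point holds as a mismatch between the sample-size and Statistical methods sections. The 102 per group depends on baseline adjustment (99 to 100 needed with it, 132 with change or follow-up scores alone), and the analysis text does not secure that adjustment for SPPB. In the least favourable form examined, power is about 81% with 102 completers, so the chance of missing a true one-point effect rises from about 9% to about 19%. With partial data from 148 randomised, power is about 86% under the assumed dropout. These figures rest on the protocol's SD and correlation, a two-sided 5% test and, for the mixed models, a correlation of 0.5 between all visits.

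The standard-error problem is a conditional risk. Type I error of a single-visit contrast is 5% if variances and correlations are truly equal, and about 3% to 10% in the illustrations. Neither the size nor the direction can be settled from the documents.

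**What to change.** In the Statistical methods section, take SPPB out of the general sentence and name one primary model that adjusts for baseline SPPB. A suitable choice is a repeated-measures mixed model on discharge, one month and three months, with baseline-by-visit and treatment-by-visit terms and an unstructured within-patient covariance. With complete data its single-visit estimate equals ANCOVA at that visit, so the 91% is kept. It uses partial follow-up without imputation, in line with the protocol's decision not to impute, and it drops the equal-variance and equal-correlation assumption. ANCOVA at the primary visit, or a constrained-baseline model with unstructured covariance, would also serve.

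Name the visit at which the primary contrast is taken. In the sample-size section, state that 102 per group assumes a two-sided, baseline-adjusted comparison at that visit.

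The cost is a few sentences in the protocol or SAP, and six covariance parameters for three visits in place of the random-intercept model's two. No extra patients, visits or data are needed. The wording should be settled before outcome data are compared by group.

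### If ANCOVA is chosen for the 1- or 3-month SPPB, the bar on imputation reduces the intention-to-treat analysis to surviving attenders and leaves discharge scores unused

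*Protocol article*

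**What the plan says.** - **Statistical methods, model.** Continuous outcomes are to be analysed by ANCOVA or by a linear mixed model with a random intercept. Neither is named as the model for SPPB.
- **Statistical methods, missing data.** "No imputation of missing data will be conducted".
- **Statistical methods, analysis set.** "The analysis will adhere to the intention-to-treat principle". The sensitivity analyses named are a per-protocol analysis and an adjustment for baseline imbalance.
- **Power of the trial.** The planned size rises from 102 to 148 per group "To account for an anticipated dropout rate of 30% during follow-up".
- **Data collection and Table 3.** SPPB, the primary outcome, is measured at inclusion, discharge, 1 month and 3 months. Mortality is a separate secondary outcome, and no rule is given for SPPB after death.

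**The concern.** An ANCOVA at a single visit uses only patients with an SPPB at that visit. With imputation barred, a patient seen at discharge but lost or dead before 3 months contributes nothing to the 3-month contrast. The result would carry an intention-to-treat label while describing only those who survived and attended.

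In acutely ill patients aged 75 and over, loss may well follow poor function. If exercise keeps weaker patients in follow-up, the contrast among attenders understates the benefit. If it loses them, the contrast overstates it. Neither named sensitivity analysis tests an assumption about missing data, and a per-protocol analysis can only remove more patients.

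**Working it through.** **1. The plan's own figure.** Inputs from the sample size section: "A significance level (α) of 5% was assumed", power 90%, a "clinically significant minimum difference of one point in the post-intervention SPPB score", "a standard deviation (σ) of 2.5 for the SPPB", and a baseline-to-follow-up correlation of 0.5. Sidedness is not stated; two-sided is assumed.

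- Unadjusted n per group = 2σ²(z₀.₉₇₅ + z₀.₉₀)²/δ² = 2 × 6.25 × (1.960 + 1.282)² / 1² = 131.3.
- ANCOVA factor 1 − ρ² = 0.75, so 131.3 × 0.75 = 98.5, or 99 per group. The plan's 102 is within 3 of this.
- Dropout: 102 / 0.70 = 145.7, or 146. The plan's 148 is within 2 of this.

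The sample size is therefore reproduced, and it is consistent with an ANCOVA on about 102 completers per group.

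**2. Who is left at 3 months.** 148 × 0.30 = 44.4 lost and 148 × 0.70 = 103.6 observed per group. Power at 102 to 104 per group is about 91%, so precision is not the issue.

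**3. Bias by loss mechanism.** Large simulated samples, SPPB SD 2.5, true effect 1.0 point, overall loss near 30%. ANCOVA on patients with a 3-month score is compared with a likelihood-type estimate that also uses discharge scores. The mechanisms, arm-specific loss rates and correlations beyond the baseline-to-follow-up 0.5 are assumptions.

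| What loss before 3 months depends on | ANCOVA | Using discharge SPPB |
|---|---|---|
| Baseline SPPB only | 1.00 to 1.01 | 1.00 to 1.01 |
| Discharge SPPB, one rule for both arms, logit slope 0.2 or 0.5 per point | 0.98, 0.92 | about 1.00 |
| Discharge SPPB, loss 37% control and 27% exercise, slopes 0.2 against 0.1 or 0.04 per point | about 0.89, 0.85 | about 1.00 |
| Same loss, slopes 0.5 against 0.25 or 0.1 per point (steep) | about 0.82, 0.74 | about 1.00 |
| Discharge SPPB, same slope, loss 20% exercise and 40% control | 0.91 | 1.01 |
| Discharge SPPB, same slope, loss 40% exercise and 20% control | 1.11 | 1.01 |
| Unseen 3-month SPPB, differing by arm (three cases) | 0.51, 0.69, 1.31 | 0.56, 0.72, 1.28 |

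The second row needs no arm-specific rule. A working treatment raises discharge scores and so changes retention by itself.

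**4. No true effect.** One rule and equal loss in both arms gives a bias of about 0, whether loss depends on baseline, discharge or 3-month SPPB. With loss of 20% and 40% driven by discharge SPPB, ANCOVA gives −0.11 or +0.10, depending on which arm loses more.

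**5. Death, illustration only.** With assumed mortality of 10% and 7% and a mean of about 7 among survivors in both arms, scoring death as 0 moves the difference by (0.10 − 0.07) × 7 = 0.21 points. The protocol gives no mortality figure.

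**The case against.** The best defence is that the plan equally permits a mixed model. That model keeps patients with a discharge score, needs no imputation and, if its covariance structure fits, is valid when loss depends on observed scores. With four visits it is the natural choice. This stands: the completers-only result follows from one of two permitted options.

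Further points also stand in part:

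- The dropout applies to follow-up, so the discharge comparison is less exposed.
- Patients with short life expectancy, or who cannot be followed up, are excluded, which limits death and loss. The 30% is nevertheless the trial's own expectation.
- A between-arm analysis of mortality is planned, so unequal survival would be visible. Its effect on the SPPB contrast would not be.
- An analysis plan that is not shown may name the model and a rule for deaths. It could not add imputation without contradicting the protocol.

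A reader might infer more than the document supports: that the plan forces a completers-only analysis, that any link between loss and function biases it, or that leaving deaths out is an error with one right correction. The first overlooks the mixed model. The second fails in the baseline-driven and shared-mechanism null cases above. On the third, a worst score for death is one debatable choice, and an article's silence on it is not a stated rule.

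**Conclusion.** The point holds as a conditional weakness that should be fixed. The stated text licenses an analysis that would drop about 44 of 148 patients per arm at 3 months, most with a usable discharge SPPB, under an intention-to-treat label. It also bars imputation in sensitivity analyses.

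When loss depends on discharge SPPB and retention differs between arms, a true effect of 1.0 is estimated at about 0.74 to 0.98, or about 1.1 with the opposite selection. The lower end rests on steep mechanisms that differ by arm; shared or milder ones give about 0.85 to 0.98. Against a minimum important difference of one point, this can matter. Using the discharge scores removes this bias. If loss depends on the unseen 3-month score, the bias can be larger and the likelihood model removes little of it, so a sensitivity analysis is needed as well.

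**What to change.** In Statistical methods:

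1. For SPPB, replace the choice of two models with one primary analysis: a likelihood-based repeated-measures model on all observed visits of all randomised patients, adjusted for baseline SPPB, with a treatment effect at each visit and a covariance structure that is not too restrictive. This is compatible with no imputation.
2. Limit the no-imputation sentence to the primary analysis. Add a multiple-imputation sensitivity analysis with a delta shift for lost patients, and report the shift at which the conclusion changes.
3. Report, as a sensitivity analysis and not as a correction, how the result changes when death counts as a worst outcome. The repeated-measures model does not settle this, because it implicitly extends SPPB past death.

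The cost is protocol wording, some programming and a longer results table. No new data are needed, and the sample size stays at 148 per group. The change should be made before unblinded analysis.

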### Patient and public involvement

The trial is designed through a collaborative dialogue involving researchers, clinicians, and healthcare managers from various disciplines. Although physical activity professionals will primarily lead the interventions, effective geriatric care requires a multidisciplinary approach to address the complex health needs of older adults, who often present with multiple concurrent health issues. This interdisciplinary and practice-oriented framework enhances the likelihood of successful intervention implementation, should they prove effective. Qualitative interviews will also be conducted with participants and their families from both the intervention and control groups to gain insights into their experiences. These interviews will take place either in the hospital during their stay or at the participants’ homes following discharge, ensuring a comprehensive understanding of their perspectives and the impact of the interventions on their health.

### Ethics and dissemination

Ethical approval for this trial has been granted by the Clinical Research Ethics Committees: “Comité de Ética De Ética De La Investigación Con Medicamentos de Navarra” (PI_2024/47; may 10, 2024; November 7, 2024), “Centro de Investigação Clínica CiC2Fs” (26.OBS.2024) and Comissió Ètica de la Investigació (02-2025-CEI-PREDISC, April 24, 2025), Data collection will be conducted with careful consideration of information requirements, informed consent, confidentiality obligations, and data utilization requirements. Participants will receive comprehensive verbal and written information about the study, and informed written consent will be obtained by the research staff prior to participation. All collected data will be pseudonymized and stored in both paper and digital formats, in accordance with the General Data Protection Regulation. Only the responsible researchers will have full access to the data. Trial findings will be disseminated through multiple channels, including scientific publications, conferences, and workshops, aimed at healthcare professionals and the public. We will adhere to the Vancouver recommendations for the authorship.

### Trial status

Participant recruitment is expected to be completed by January 2026. Data collection is scheduled to conclude in March 2026, and the study results are anticipated to be available by June 2026. Any deviations from this protocol will be updated on ClinicalTrials.gov, and changes will be reported when disseminating the results.

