### Inclusion and exclusion criteria

Participants in this study will be older adults aged 75 years and above who are hospitalised in the Geriatrics and Internal Medicine departments for medical conditions. The inclusion criteria require participants to be able to ambulate with or without assistance, capable of providing informed consent or having a legal representative, and currently hospitalised due to a medical condition. Participation in the study is voluntary, and patients who do not wish to participate will not have their usual medical care affected. Conversely, individuals will be excluded if they have a life expectancy of less than three months, suffer from terminal illnesses, cannot participate in a multicomponent exercise program, exhibit moderate to severe cognitive impairment (Global Deterioration Scale, GDS, stages 6–7), or demonstrate moderate to severe disability (Barthel Index < 60). The eligibility criteria are presented in Table 1. Randomisation will be performed using an online random number generator to ensure the unbiased allocation of participants to the intervention and control groups (randomizer.org).

**Table 1 pone.0332391.t001:** Eligibility criteria.

INCLUSION CRITERIA	• ≥ 75 years old hospitalized in European Geriatrics and Internal Medicine services (HUN, HDFF and HNSM) • Expected hospital stay > 6 days
EXCLUSION CRITERIA	• Refusal to sign the informed consent by the patient/primary caregiver/legal guardian or inability to obtain it. • Life expectancy of less than 3 months or oncologic or non-oncologic disease in terminal phase. • Impossibility of follow-up. • Inability to participate in a multicomponent exercise program. • Medical contraindication to exercise. • Moderate-severe stage neurocognitive disorder GDS – Fast Reisberg 6–7 • Moderate-severe disability (measured by Barthel Index (BI < 60).

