### Intervention

Patients in the control group will receive standard care currently provided to all patients, including referrals to physiotherapy as needed. The recruitment start date will be January 2025 in Spain, and September 2025 in Andorra and Portugal, and the expected end date is June 2026. In contrast, the intervention group will participate in a structured multicomponent exercise program, which will encompass progressive and supervised training combining aerobic resistance, strength, and balance over a duration of 4 days during their hospitalisation. The multicomponent training protocol is presented in Table 2. This program will be overseen by trained and experienced professionals on the research team, and upon discharge, participants will receive individualised guidelines for continuing the multicomponent exercise program for three months, along with personalised nutritional recommendations.

**Table 2 pone.0332391.t002:** Multicomponent training protocol.

WARM UP								
Stationary bicycle*						**Chair squats***		
5 min (Borg 3–4)						3 sets x 10 rep.		
RESISTANCE TRAINING*								
Exercises								
Leg press – Seated bench press machine – Leg extension								
PROGRESSION WEIGHT PROTOCOL								
Assessment	**V0**					**V1**	**V2**	**V3**
Session	1RM	**S1***	**S2***	**S3***	**S4***	1RM	1RM	1RM
Sets		2	3	3	3			
Repetition		10	10	10	8			
(% 1RM)		40	50	60	70			
Rest (sec)		120 between sets and exercises						
BALANCE: Core and Hip stability*								

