***Only Intervention Group.**

**V0: visit 0; V1: visit 1; V2: visit 2; V3: visit 3; S1: session 1; S2: session 2; S3: session 3; S4: session 4.**

The multicomponent exercise program will include chair squats (sit-to-stand exercise). The main training phase will use machines for strength training targeting major muscle groups: the lower extremities (such as leg press and knee extension) and one exercise for the upper extremities (seated chest press). The objective is to perform 2–3 sets of 8–10 repetitions at an intensity of 40–70% of one repetition maximum (1RM), tailored to everyone’s functional capacity. Each training session will also incorporate hip abduction exercises, balance exercises, and stretching routines, ensuring a comprehensive approach to enhance health and mobility among participants. A daily logbook will be used during the hospital stay to register the exercise sessions performed for the intervention group, as well as treatment safety.

Patients will be followed up for 3 months, and there will be coordination between the exercise program in the hospital and primary care (Fig 3).

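### The Trial status dates end data collection before patients enrolled in January 2026 reach the 90-day SPPB, and the Intervention section gives a different end date

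*Protocol article*

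**What the plan says.** Three parts of the protocol article bear on the calendar.

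- **Trial status.** Recruitment and data collection close two months apart: "Participant recruitment is expected to be completed by January 2026. Data collection is scheduled to conclude in March 2026". Results are anticipated by June 2026.
- **Intervention.** Start dates are staggered by country: "The recruitment start date will be January 2025 in Spain, and September 2025 in Andorra and Portugal". The same sentence continues that "the expected end date is June 2026". It does not say whether this ends recruitment, follow-up or the whole study.
- **Follow-up schedule.** The Abstract and the Data collection section place SPPB, the primary outcome, at discharge and at 30 and 90 days (one and three months) after discharge. Table 3 lists it at Visit 3. The text under Table 2 says "Patients will be followed up for 3 months". Because the clock starts at discharge, the stay comes first, and Table 1 requires "Expected hospital stay > 6 days".

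The sample size section plans about 50 patients per group at each of three hospitals, 300 in all. The Statistical methods section rules out imputation of missing data.

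**The concern.** The gap between the latest recruitment date and the latest data-collection date is shorter than the stay plus 90 days. If both dates were kept, patients enrolled late would have no 3-month SPPB, for reasons that have nothing to do with their health or their willingness to attend.

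The hospitals in Portugal and Andorra have a short recruitment period, so a fixed block of late enrolment days is a larger share of their patients than of Spain's. The Introduction names validation in an international setting as an aim. The 3-month comparison would therefore be thinnest at the sites that serve that aim. Visits not held cannot be recovered later, and the plan does not impute.

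**Working it through.** The article states no figure for patients lost to the calendar, so there is none to reproduce. The check uses its dates and quotas.

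**Inputs from the article**
- Recruitment starts January 2025 (Spain) and September 2025 (Portugal, Andorra); the first of the month is used.
- Recruitment ends by January 2026, no day given; 31 December to 31 January tested.
- Data collection ends March 2026, no day given; 31 March is the most favourable reading.
- Last SPPB is 90 days after discharge.
- 100 patients per hospital (50 per group).

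**Assumptions**
- Stay of 7 days from enrolment (Table 1 requires an expected stay above 6 days); 0 and 10 also tested.
- Uniform accrual within each hospital.

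**Step 1: when day 90 falls**
- Zero-day stay, enrolled 1 January 2026: 1 January + 90 = 1 April 2026.
- 7-day stay, enrolled 1 January: discharge 8 January, day 90 on 8 April.
- 7-day stay, enrolled 31 January: discharge 7 February, day 90 on 8 May.

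**Step 2: last enrolment that fits**

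31 March 2026 − 90 days = 31 December 2025 (last discharge). Less 7 days, this gives 24 December 2025 (last enrolment).

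**Step 3: patients losing the visit**

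Per hospital: 100 × (recruitment days after 24 December) / (total recruitment days).

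| Recruitment ends | Late days | Spain | Portugal and Andorra, each | Total of 300 |
|---|---|---|---|---|
| 31 Dec 2025 | 7 | 7/365 = 1.9% | 7/122 = 5.7% | 13 (4.5%) |
| 1 Jan 2026 | 8 | 8/366 = 2.2% | 8/123 = 6.5% | 15 (5.1%) |
| 15 Jan 2026 | 22 | 22/380 = 5.8% | 22/137 = 16.1% | 38 (12.6%) |
| 31 Jan 2026 | 38 | 38/396 = 9.6% | 38/153 = 24.8% | 59 (19.8%) |

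**Step 4: sensitivity, recruitment to 31 January**
- Stay of 0 days: 31 late days, 16.1%. Stay of 10 days: 41 late days, 21.3%.
- Equal daily rate at all hospitals instead of 100 each: 3 × 38 / (396 + 153 + 153) = 16.2%.
- Data collection closing on 1 March: 24% to 35% with a 7-day stay, for recruitment ending between 1 and 31 January.

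**Step 5: the other visits**

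For a 31 January enrolee discharged on 7 February, day 30 is 9 March. With an end-March close, the discharge and 1-month assessments fit.

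**Step 6: what June 2026 could mean**
- End of follow-up: the latest day 90 (8 May) fits and the loss is zero, but the March date in Trial status is then wrong.
- End of recruitment: this contradicts January 2026 and the conflict is worse. A 30 June enrolee reaches day 90 on 30 June + 7 + 90 days = 5 October 2026.
- End of the study overall, matching the date for results: the two sections agree, but the March close and its conflict with the 90-day visit remain.

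**The case against.** The strongest reply is that nothing in the article orders follow-up to stop. Trial status is a forecast, given to the month, while the operative sections require the 3-month visit for every patient. In practice the closing date would probably slip, and the article says deviations will be updated on the registry and reported. From 31 December to 31 March is exactly 90 days, so the forecast may simply have rounded to whole months and left out the stay. This stands as a reason not to predict that visits will be lost. It does not make the dates compatible: even recruitment ending on 31 December overruns by about a week with a 7-day stay.

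Two stronger readings are tempting.

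- **A reader might infer that a fifth of patients will lose a primary assessment.** The documents do not support that as an unconditional figure. It needs recruitment through 31 January, a 31 March close, uniform accrual, full quotas at each hospital and a 7-day stay. The June 2026 date admits a reading with no loss at all.
- **A reader might infer that the calendar loss consumes most of the 30% dropout allowance.** That ignores overlap. If dropout is independent of enrolment date, 30% of the 59 would be lost anyway, and the net extra loss is 0.70 × 59 = 41 of 300, about 14%. That leaves 150 × 0.70 × 0.802 = 84 per group at 3 months, against the 102 the plan requires. With its inputs (difference 1, SD 2.5, correlation 0.5) and a two-sided, baseline-adjusted comparison, power at that visit is about 85% instead of 90%. This is the case with recruitment to 31 January, at one of three post-baseline time points.

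The loss is also set by enrolment date, not by arm, so it is not a route to bias between the groups.

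**Conclusion.** The point holds as a conflict of dates. As written, the Trial status schedule cannot accommodate the 90-day SPPB for any patient enrolled in January 2026, whatever the length of stay, and the June 2026 date in the Intervention section does not settle which date governs.

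If the Trial status dates were followed with a 31 March close, the share losing the 3-month SPPB would run from about 4–5% to about 20%, depending mainly on the day recruitment ends, under the accrual and stay assumptions above. At the upper end the loss is about 25% at each hospital starting in September 2025 and about 10% in Spain. The harm would be to precision and site representation at 3 months. That the documents conflict is certain; that visits would be lost is conditional on the March date being enforced.

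**What to change.** Define the end of data collection by the last patient instead of a calendar month: last discharge plus 90 days plus the visit window. If recruitment runs through January 2026, day 90 for a 31 January enrolee with a 7-day stay is 8 May, so this means mid-May 2026 or later. State in the Intervention section what June 2026 refers to, and make it agree with Trial status. If it is the end of recruitment, the January, March and results dates in Trial status all have to move.

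The cost is a date change in the protocol and on the registry. With recruitment ending in January, results come about 1–2 months later. No extra patients are needed.
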